| Research                                                                                                                                                                                                                                                                                                                                                                                                                            |                             |                      |
| Aims iv                                                                                                                                                                                                                                                                                                                                                                                                           |                             |                      |
| To describe the range of airway inflammatory infiltrate in a group of patients with mild to moderate COPD, and to relate that cell picture to the response to ICS therapy over a 6 month period.                                                                                                                                                                                                                                    |                             |                      |
| The Hypothesis is that positive benefit of ICS therapy in COPD patients is most marked in those with the most prominent degree of airway eosinophilia.                                                                                                                                                                                                                                                                              |                             |                      |
| Justification v                                                                                                                                                                                                                                                                                                                                                                                                   |                             |                      |

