#### Study outcome measures/efficacy measurements

- Changes in the QOL measure and spirometric values (large and small airway flow rates)
- Sputum neutrophil and eosinophil percentage counts
- Bronchoalveolar lavage cell differential counts and FACS analysis (lymphocyte and macrophage subtypes and activation markers). BAL supernatant will be stored for cytokine and chemokine assays and assay of selected mediators, eg ECP, neutrophil elastase and myeloperoxidase.
- Airway biopsies: the initial emphasis will be on acute and chronic cellular inflammation: numbers of eosinophils, neutrophils, lymphocytes and macrophages and activation markers HLADR and CD25 but with the potential for later study of indices of scarring and "remodelling" of the airway wall ie collagen I, III and V deposition, epithelial integrity, subepithelial basement membrane thickness and degree of vascularity in the subepithelial lamina propria area (by collagen IV staining).

**NB** Over the past 15 years of research into airway pathology using fibre-optic bronchoscopy, we have developed a wide range of end points with which to assess both BAL and biopsy material. The degree to which we can fully utilise the material will depend upon funding over the next three years. However, we already have sufficient funding to allow assessment of acute and chronic cellular infiltrates in the airway, which is our primary pathological endpoint. Further grant applications will be developed over the next 12-18 months, based upon this study protocol, the extremely valuable biological material obtained and our extensive "track record" in this field of research (see references).

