#### Statistical Analysis

At the end of the study we will intend to have 24 paired sets of data in volunteers treated with active intervention (Fluticasone) and 12 in placebo treated controls.

There will be 4 main approaches to analysis:

- Baseline bronchoscopic data as a whole will be analysed against our current historic normal control data, of which we have large numbers both for airway biopsy (n=24) and BAL (n=36). This will give us excellent power to detect even subtle changes within COPD cell profiles (and later structural components).
- The placebo control material will be used to establish stability over time in biological signals and to establish coefficients of repeatability for cellular indices. Paired analysis within the actively treated group will be undertaken to indicate which cellular populations or activation markers may be susceptible to change with ICS, and then changes over time in these indices will be compared with respective changes in the placebo treated control material. We have previously published repeatability data in chronic stable asthmatics, and done similar calculations in post lung transplant airway samples, which indicate that optimal power for detecting changes with time is achieved with approx. 15 data pairs for most cell lines. With the numbers available in this COPD study, we therefore have substantial "reserve".
- The central analysis will focus on the ICS treated group and use changes over time in both cellular indices (in BAL and biopsies) and clinical and physiological end points, and undertake regression analyses to define which, if any, of the cellular changes are related to clinical and/or physiological improvements.

- We will perform post-hoc analyses in selected sub-groups, namely:
  - a) those in whom regular sputum production is a feature.
  - b) those with above normal airway eosinophils.
  - c) those with more or less severe lung function abnormalities (best and worse 10) to define whether ICS have more benefit in these patients than in COPD in general.

This will be a large and complex data set, but we have extensive experience in relating clinical, physiological and bronchoscopic pathological end points. We have developed close collaboration with [name] and [name], our statistical advisers at Monash University, and they will again by providing assistance with this study.

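### The hypothesis concerns the degree of airway eosinophilia, but the only listed analysis relating eosinophil level to steroid benefit is a post-hoc yes/no subgroup

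*Protocol*

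**What the plan says.** The Aims section sets out to describe the airway infiltrate and "to relate that cell picture to the response to ICS therapy over a 6 month period". The hypothesis that follows is that "positive benefit of ICS therapy in COPD patients is most marked in those with the most prominent degree of airway eosinophilia".

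Statistical Analysis lists four approaches:

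1. Baseline bronchoscopic data are compared with historic normal controls.
2. Repeatability is assessed in the placebo arm. Changes within the active arm are then examined and compared with those on placebo.
3. The third is the main one: "The central analysis will focus on the ICS treated group and use changes over time in both cellular indices (in BAL and biopsies") together with clinical and physiological end points, in order to find which cellular changes go with improvement.
4. The fourth opens "We will perform post-hoc analyses in selected sub-groups, namely", and item (b) is "those with above normal airway eosinophils". A closing clause, printed after item (c), gives the purpose: to see whether ICS help these patients more than COPD patients generally.

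Item (b) states no numerical limit, no compartment (biopsy, lavage or sputum) and no time point; I read it as referring to baseline. The outcome list records eosinophils numerically, for example "Sputum neutrophil and eosinophil percentage counts" and cell numbers in biopsies. The planned completers are 24 on fluticasone and 12 on placebo.

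**The concern.** The hypothesis makes the degree of eosinophilia the predictor of benefit. None of the four approaches relates that degree, measured before treatment, to the response to ICS. The third is a regression, but its predictor is the change in cells during treatment. A fall in eosinophils on ICS is not the same quantity as how eosinophilic the patient was at the start. That leaves item (b), which reduces a measured count to above normal or not.

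Under such a split, a patient just over the limit counts the same as the most eosinophilic patient in the trial, and one just under it the same as a patient with none. If benefit really is graded, information is lost in a trial with only 36 completers. Because the allocation is 2:1, the split may also leave very few eosinophilic patients on placebo, and without them the treatment difference in that group cannot be estimated usefully.

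**Working it through.** **Inputs from the protocol.** There are 24 + 12 = 36 completers, which agrees with the 2:1 allocation, and with 45 recruits if 20% are lost (36/0.80 = 45). The protocol states no alpha, power, effect size, SD, eosinophil distribution or expected share above normal, so it has no figure of its own to reproduce for this analysis.

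**Assumptions, mine.** Log eosinophils are normal, benefit is linear in them, residual SD is 1, and tests are two-sided at 5%. The share above normal, p, is varied.

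**Step 1: information kept by the split.** This is the squared correlation between the marker and its yes/no version, φ(c)²/[p(1−p)], where c is the cut with share p above it. For p = 0.25, c = 0.674 and φ(c) = 0.318, so 0.318²/(0.25 × 0.75) = 0.54.

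| Share above normal | Kept | Lost |
|---|---|---|
| 50% | 0.637 | 36% |
| 35% | 0.603 | 40% |
| 25% | 0.539 | 46% |
| 15% | 0.426 | 57% |

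**Step 2: sensitivity of that range.** With a normal marker and only 5% above the limit, the loss is 78%. With 50% down to 10% above the limit, and benefit linear in the raw marker, the loss is 25-73% (uniform), 35-52% (exponential), 39-49% (lognormal, sigma 0.5) and 46-73% (lognormal, sigma 1). The overall range is therefore about 25-78%.

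**Step 3: power of a treatment-by-eosinophil test, 24 v 12, by simulation.** The slope is the extra benefit on ICS per SD of log eosinophils. In the last row, benefit is a step at the limit of normal with the same standardised size, 1.3.

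| True relation | Continuous form | Split, with 50%, 35%, 25%, 15% above normal |
|---|---|---|
| Linear, slope 1.3 | about 88% | 65%, 59%, 50%, 34% |
| Linear, slope 0.6 | 33-35% | falls from about 23% to about 13% |
| Step at the limit, size 1.3 | 64%, 59%, 52%, 39% | 92%, 91%, 87%, 75% |

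Slope 1.3 is an extreme gradient: it implies a correlation within the ICS arm of 1.3/√(1 + 1.3²) = 0.79. Slope 0.6 implies 0.6/√(1 + 0.6²) = 0.51, and at that slope both forms have low power.

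**Step 4: few eosinophilic patients on placebo.** The chance of at most 1 of 12 above normal is (1−p)¹² + 12p(1−p)¹¹. For p = 0.25 this is 0.032 + 0.127 = 0.158, or 16%. For p = 0.15 it is 0.142 + 0.301 = 0.443, or 44%.

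**The case against.** The strongest reply has four parts.

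- **The hypothesis can be read as a threshold.** It speaks of patients at the upper end, which fits a step as well as a slope, and under a true step the split wins (last row of the power table). This stands. It limits the size of the point and means the split should not be deleted. It does not show that a yes/no form alone is adequate, because the hypothesis is worded by degree and the protocol gives no reason to place a step at the limit of normal.
- **The analysis is exploratory, and no above-versus-below test or interaction is specified.** This is true, and the power figures therefore illustrate what such a test would do; they do not describe a planned test. But item (b) is the only listed analysis that uses eosinophil level to ask who benefits, so its form matters.
- **Functional form belongs in the analysis plan.** An omitted cut-off or compartment would indeed be no finding. Here, however, the protocol itself names the form, and an analysis plan that followed it would inherit the split.
- **Sample size dominates.** At slope 0.6 the continuous test would usually miss the gradient too. This stands.

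Three stronger readings are tempting and are not supported. A reader might infer that the hypothesis and item (b) assign different patients to an eosinophilic group, but a graded variable defines no group. A reader might infer that the limit must come from "our current historic normal control data, of which we have large numbers both for airway biopsy (n=24) and BAL (n=36"), leaving sputum unclassifiable. Those data are cited for the first approach and are never tied to item (b). And a reader might conclude that a real gradient would be missed solely because of the cut, which the low power of either form at a moderate slope rules out.

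**Conclusion.** The mismatch is real and lies in the protocol's own text: a hypothesis stated by degree is matched only by a post-hoc yes/no subgroup, and the central regression answers a different question.

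The loss of about 36-57% is conditional on a linear relation with log eosinophils, normality on that scale and 15-50% of patients above normal. It is not a property of the trial's data, and it applies to item (b) alone, since the central regression uses cellular changes on their own scale. With other shapes or shares, the range is about 25-78%. If benefit is a step at the limit of normal, the ranking reverses. The risk of an almost empty eosinophilic placebo group (16% or 44%) depends only on the share above normal.

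This is a change worth making because it costs almost nothing. It does not repair the low power for a moderate gradient, and it is not a fatal flaw.

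**What to change.** In the fourth approach of Statistical Analysis, at item (b), add as the main eosinophil analysis the baseline airway eosinophil count as a continuous variable in one named compartment, for example log(count + 1) of biopsy eosinophils. Estimate how the ICS-placebo difference in response changes along it, and report that estimate with its confidence interval and the predicted difference at low, middle and high counts. Keep the above-normal split as a secondary display, stating its compartment, its limit and where the limit comes from.

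The cost is a sentence or two of wording, with no new patients, samples or measurements. The downside is that the continuous form assumes a roughly linear trend and loses power if the true relation is a threshold, so the shape should be checked with a plot or a rank-based version.

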## SUBJECTS

### Selection of subjects x

#### Inclusion criteria:

- Age 40-70 years
- 36 subjects with smoking-related COPD to complete the study, which will mean likely need for initial recruitment of up to 45 patients (both male and female will be included).
- Minimum of 15 pack-year history of cigarette smoking. Either current or ex smokers.
- FEV1 40% to 80% predicted and/or FEF50<50% with FER (ratio of FEV1 to FVC)  $\leq 70\%$  post bronchodilator and definite scalloping out of the descending limb of the flow-volume loop on spirometry. Absolute FEV  $\geq 1.5$  litres.
- Bronchodilator therapy with a short acting beta agonist prn and anticholinergics in stable doses will be allowable.

#### Exclusion criteria:

- A history of asthma, either by doctor's diagnosis or with classic clinical features ie episodic wheezing relieved by bronchodilator, typical diurnal variation of symptoms of chest tightening, wheeze and breathlessness, and these classic symptoms precipitated by specific exposure to "trigger factors" such as dust, fumes and exercise. If there is doubt about diagnosis, this will be decided through consensus by at least 2 of the clinician investigators.
- A history of symptomatic cardiovascular disease or significant renal/hepatic disease or diabetes mellitus. An ECG will be performed and must lack ischaemic changes.
- Warfarin therapy and/or a low platelet count ( $< 120$ ).
- Use of oral corticosteroid or ICS medication in last 3 months before recruitment.
- Use of long acting  $\beta$  agonist in past 4 weeks.
- Upper respiratory tract infection or acute exacerbation in past 4 weeks.
- Oxygen saturation  $\leq 92\%$  at rest i.e.: excluding ventilatory failure.

### Recruitment of subjects xi

For the RHH limb of this study, subjects who have previously been involved in smoking cessation studies, or specifically in studies of COPD and who are on the Dept of Respiratory Medicine database of volunteers will be approached by phone or letter. In Melbourne, recruitment was by advertisement in the press or in public places, but it is not envisaged at this stage that such strategies will be necessary in Tasmania.

### Information about subjects

(i) State whether information will be identified, potentially identifiable or unidentified. xii  
All individuals will be identified to the sponsor by initials and identification number only. Patients will be informed in the plain language statement that their hospital based research record may be viewed by the sponsor or other regulatory bodies – but for source verification only.

(ii) State source(s) of information. xiii

Information will be available from records of previous clinical and physiological assessments held by the Dept of Respiratory Medicine.

(iii) Will data on individual subjects be obtained from any Commonwealth Government agency? xiv  
If so, name agency. NO.

**Potential risks xv**

The main issue in this study is undertaking bronchoscopy in a volunteer population. However, [name] research team has a long track record of bronchoscopic research in asthma, lung transplant recipients, and more recently in COPD patients. Overall, [name] has been CI and had overall responsibility for approx. 600 research bronchoscopic procedures in the past 15 years.

In terms of lung function, this group of COPD patients will be comparable to or even less impaired than many subjects studied over the past 15 years. We will not be including any patient with an FEV1 of < 1.5 litres, which is likely to be > 50% predicted in all subjects. Subjects will be premedicated with  $\beta$ -agonist and anticholinergic bronchodilators and oxygen saturation will be monitored. Supplemental oxygen will be given routinely.

**Post contact xvi**

Patients are to be phoned 1 week after final cessation of study medication to check on clinical stability. If there has been any suggestion of deterioration, the individual will be invited to the RHH for clinical review.

**Remuneration xvii**

Subjects will be reimbursed travel expenses, and it has been our policy in such studies to offer \$100 for compensation for time and discomfort for each bronchoscopy.

**Confidentiality and anonymity xviii**

All documents pertaining to the study will be securely locked in the Dept of Respiratory Medicine research room during the period of the study, and available only to the research team. They will then be kept for 15 years, after which time they will be destroyed under supervision. Due to space constraints it is likely that the documents will be archived outside the hospital by the sponsor, but with access limited to the CI only. There will be no electronic data collected for this study.

**Administration of substances/agents xix**

Fluticasone propionate, 500 mcg bd, or identical placebo medication, will be taken by the patients from a dry powder "Diskus" device for a duration of treatment of 6 months. This is a fully licenced inhaled corticosteroid with an excellent safety profile at this dose and taken in this way.

**Human tissue or body fluid sampling xx**

1. Sputum, either produced spontaneously or induced by hypertonic saline inhalation in a standard way. This is processed to provide smears on slides for cell counting and separation of the liquid component for storage and future analysis of mediators.
2. Bronchoalveolar lavage (3X60 ml aliquots) for analysis of cells and solutes.
3. 6 endobrachial biopsies taken with cupped forceps (1-2 mm^3) for tissue processing for analysis of inflammatory cells, fibrosis and angiogenesis using image analysis.

**Other ethical issues xxi**

At the end of the clinical study, hopefully at the end of 2002, we will transfer all the archived biopsies and slides (BAL and sputum) and stored sputum and BAL supernatants to Hobart from Melbourne for further analysis. We will eventually wish to perform comprehensive analysis of these samples for inflammation and markers of airway scarring and remodelling. This work will form the basis of an NHMRC grant application in 2003

**Information sheet xxii**

Attached.

**Consent form xxiii**

Attached.

